The occupational therapist and activity worker work with staff in the unit daily for the rest of the five weeks to model and give intensive, hands on support for staff to gain confidence in the implementation of the techniques and interventions learned during the training course. The reinforcing stage starts during the fifth week, when the GetREAL team facilitates a half day workshop to review the intervention with the service manager and staff and agree how best the skills acquired can be incorporated into the unit’s usual structures and processes. An Action Plan reflecting this is drawn up by the GetREAL team’s occupational therapist and a member of staff is identified who will oversee delivery of the Action Plan in the unit after the GetREAL team have left. Email support to the unit is available from the GetREAL team over the next 12 months. If no contact is made by the unit, a prompt email is sent by the GetREAL team occupational therapist every six months during this period to encourage contact.

Comparison units: Units allocated to this arm continue with their usual service and are able to use any resources at their disposal to provide maximum care for service users. There are no restrictions on the work of these teams.

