### Treatment fidelity

At the end of each unit’s intervention, the supervising occupational therapist completes a proforma together with the staff training teams’ occupational therapists and a senior member of the research team who attended the predisposing meetings. This proforma records the delivery of 24 specific aspects of the GetREAL intervention. Each item completed achieves a score of 1, giving a total possible score of 24 (see Table 1).

**Table 1 T1:** GetREAL staff training intervention fidelity assessment

**Get REAL intervention component**	**Completed (Y/N)**

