**Sustainability and Reinforcing Phase**	
At the end of the 5 weeks, a written action plan for the unit to continue the GetREAL work for the next 12 months is agreed	
The 12 month action plan is circulated to all unit staff by the GetREAL team	
At the end of the 5 weeks, activity is included in at least 50% of SUs’ individual care plans	
A link person is identified to keep email contact with the GetREAL team/steering group members for up to 12 months	
GetREAL team/steering group members make email contact at least twice with the unit in the 12 months following the 5 week visit	
The link person contacts the GetREAL team at least once during the 12 month period	

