### Secondary outcomes

i) Service users’ social functioning as rated by a key staff member using the Life Skills Profile [32]. This measure comprises 39 staff rated items each rated on a four point likert scale with the most positive response scoring 4 and the least scoring 1, giving an overall score ranging between 39 and 156.

ii) length of admission

iii) percentage of service users discharged/ready for discharge in the last 12 months

iv) percentage of service users discharged to an out of area placement in the last 12 months

v) staff attitudes towards service user’s progress are assessed using the question “I expect this person to be able to move on to a more independent setting within the next 12 months”. The response is in the form of a five point likert scale.

vi) service quality as assessed using the Quality Indicator for Rehabilitative Care (QuIRC) [24], [25]. This tool comprises 145 questions on service quality and provision (e.g. number of beds, average length of stay, treatments and interventions, staffing, staff turnover, training and supervision, links with community resources such as colleges, employment agencies and leisure facilities, service user involvement in care planning and running the unit, promotion of service users’ independent living skills, the protection of service users’ human rights such as privacy and dignity, legal rights and the use of restraint and seclusion. The QuIRC gives percentage ratings on seven domains of care: Living Environment, Therapeutic Environment, Treatments and Interventions, Self-management and Autonomy, Social Interface, Human Rights and Recovery Based Practice.

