### Baseline data

Descriptive data on all service users are collected from staff and case notes as follows: demographics (age, gender, ethnic group); diagnosis; length of history; length of current admission. Primary and secondary outcomes measures are completed as described above. Potential mediators of outcomes are assessed including the staffing of the unit, recorded from the unit manager, service users’ substance use, assessed using the staff rated Clinician Alcohol and Drug Use Scales [33] and challenging behaviours which may make community placement difficult, assessed using the staff rated Special Problems Rating Scale [34].

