### Statistical analysis

The baseline characteristics of the service users will be summarised using mean (SD), median (interquartile ranges) or proportions as appropriate and compared across the trial arms descriptively. Random effects linear regression will be used for the primary outcome adjusted for the baseline value of the Time Use Diary score to evaluate the effect of the intervention. Some of the service users will be different to those present at baseline as some present at baseline will have been discharged and new service users will have been admitted. Therefore, the mean baseline score calculated for each unit (based on the service users present in the unit at the baseline data collection time point) will be used in the model rather than the scores for the individual service users. Bias due to missing data and predictors of missingess will be investigated. The analysis will be adjusted for the predictors of missingness that are associated with the outcome if required, to preserve the missing at random mechanism in the data. Assumptions of normality of the residuals will be investigated. For service users with missing primary outcome data (due to lack of capacity to give informed consent to participate in the interview), the agreement between the staff and service user Time Use Diary scores will be examined by plotting the two scores against each other. If the data roughly form a straight line, then the staff diaries will be substituted for the service users’ diaries as part of a sensitivity analysis. Otherwise the missing Time Use Diary scores will be imputed using multiple or regression imputation. A sensitivity analysis will also be carried out adjusting for the length of admission in the unit at the 12 month follow-up and the GetREAL intervention fidelity score.

For the secondary outcomes, appropriate statistical models allowing for clustering will be used for outcomes measured at the service user level and appropriate statistical tests based on the cluster summary measures will be used for outcomes measured at the unit level. The results from the secondary analyses will be treated as exploratory and only estimates and confidence intervals will be reported. All analyses will be carried out on an intention to treat basis.

A full statistical analysis plan will be developed by the study statisticians in collaboration with the research team and ratified by in Independent Trial Steering Group nearer the analysis stage.

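### The sensitivity analysis adjusts the arm comparison for a fidelity score that is undefined in comparison units and for length of admission at follow-up, so its arm coefficient should not be read as the treatment effect

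*Protocol article*

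**What the plan says.** Under Statistical analysis, the primary model is a random effects linear regression of the Time Use Diary score at follow-up, adjusted for the unit's mean score at baseline. A further sensitivity analysis is named, "adjusting for the length of admission in the unit at the 12 month follow-up and the GetREAL intervention fidelity score". The same section puts all analyses on an intention-to-treat footing and leaves the full statistical analysis plan to be written later.

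The Treatment fidelity section defines the score: "This proforma records the delivery of 24 specific aspects of the GetREAL intervention", one point each, up to 24. Every item in Table 1 describes something done by or with the GetREAL team. For the other arm, Study interventions says "Units allocated to this arm continue with their usual service". Neither section gives comparison units a score or a rule for coding one.

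Length of admission appears twice elsewhere. Secondary outcomes lists it as "ii) length of admission", followed by "percentage of service users discharged/ready for discharge in the last 12 months". Baseline data records "length of current admission" for service users present at baseline. The sensitivity analysis uses the follow-up value.

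**The concern.** A sensitivity analysis of a treatment effect is useful when it estimates the same effect under a different, reasonable assumption. Neither covariate clearly allows that.

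Fidelity is a property of the intervention arm alone and arises after randomisation. In a model that also contains arm, it either cannot be used for half the units or takes over part of what the arm term should measure. If the training works through the components that the score counts, adjusting for the score removes the effect under study.

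Length of admission at follow-up is also measured after randomisation. The Discussion part of the Abstract presents the training as having potential to reduce the need for hospital treatment and to support discharge, so the protocol itself allows that stay may respond to the intervention. Conditioning on it may remove part of the total effect or distort it.

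The risk is one of interpretation. A genuine benefit could be reported as disappearing on adjustment, or the adjusted result could be too imprecise to say anything.

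**Working it through.** **Inputs.** From the article: 40 units randomised equally, so about 20 per arm; average cluster size 12; ICC 0.04; target effect 0.35 SD; 80% power; fidelity range 0 to 24. Assumed, because the article does not give them: two-sided alpha of 0.05, and a fidelity mean of 16 to 20 with SD 2 to 4 in intervention units. The check works on unit means and omits the baseline covariate.

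**The plan's own figure.** Two means at 0.35 SD and 80% power need 129 per arm. The design effect is 1 + (12 − 1) × 0.04 = 1.44. Then 129 × 1.44 = 185.8, rounded up to 186 per arm, and 372 / 12 = 31 units. This reproduces the article and is not in dispute.

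**Fidelity left missing in comparison units.** All comparison units drop out, and no arm contrast can be estimated.

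**Fidelity coded 0 in comparison units.** The fidelity slope is then estimated only within the intervention arm, and the arm coefficient is the intervention-arm line extended back to a score of 0, minus the comparison mean. Relative to the model without fidelity:

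SE ratio = sqrt{[1/20 + 1/20 + mean²/(19 × SD²)] / [1/20 + 1/20]}

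- Mean 20, SD 2: sqrt[(0.1 + 400/76)/0.1] = 7.3
- Mean 20, SD 3: sqrt[(0.1 + 400/171)/0.1] = 4.9
- Mean 18, SD 3: sqrt[(0.1 + 324/171)/0.1] = 4.5
- Mean 16, SD 4: sqrt[(0.1 + 256/304)/0.1] = 3.1

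**What the coefficient estimates.** With a true effect of 0.35 SD at mean fidelity and a within-arm slope b per point, its expected value is 0.35 − b × mean. A slope of 0 gives 0.35. A benefit proportional to fidelity (b = 0.35/mean) gives 0. A slope of 0.03 gives 0.35 − 0.60 = −0.25 at mean 20, and 0.35 − 0.48 = −0.13 at mean 16.

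**Simulation** (20 units per arm, 12 users each, 4,000 data sets per row and slope, scores rounded and capped at 24):

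| Fidelity mean, SD | Arm coefficient, slope 0 | Proportional benefit | Slope 0.03 | SE ratio |
|---|---|---|---|---|
| 20, 2 | 0.34 | 0.02 | −0.26 | 7.6 to 7.9 |
| 20, 4 | 0.35 | 0.01 | −0.24 | 4.3 to 4.5 |
| 16, 4 | 0.35 | 0.00 | −0.13 | 3.1 to 3.3 |

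Without fidelity in the model, the mean estimate was 0.34 to 0.35 with an SE of about 0.11. With it, the SE was 0.36 to 0.88, and the correlation between arm and fidelity was 0.95 to 0.99. At the favourable end, a 95% interval is about ±1.96 × 0.36 = ±0.7 SD, twice the target effect.

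**Length of admission.** In a linear model, the arm coefficient after adjustment equals the total effect minus g × d. Here d is the difference in mean stay at follow-up that the intervention causes, and g is the slope of the outcome on stay. If d = 0 there is no shift. The article gives neither quantity, so no size can be attached.

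**The case against.** Four replies deserve weight.

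First, missing and raw zero are not the only codings. Fidelity could be centred within the intervention arm, with 0 given to comparison units. The mean term in the formula is then 0, the SE ratio is sqrt(0.1/0.1) = 1, and the arm coefficient is the effect at average fidelity. This stands. A reader might infer that any fidelity-adjusted estimate is meaningless, and that goes too far. But centring leaves the arm effect essentially as it was, so the model informs only about the fidelity slope, which the intervention units alone can supply. The article also does not specify centring.

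Second, a reader might infer that the analysis must mislead whatever the truth. It need not. With raw-zero coding the estimate stays at 0.34 to 0.35 if fidelity has no bearing on outcome, although it is very imprecise.

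Third, residents at follow-up partly differ from those at baseline, and some of their stay may pre-date randomisation. Adjusting for it is a natural wish and biases the total effect only if the intervention changes stay or discharge. This too stands, so the length-of-admission point is the milder of the two.

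Fourth, Table 1 includes an item such as "The link person contacts the GetREAL team at least once during the 12 month period", while the proforma is completed when a unit's intervention ends. A reader might infer that the full 24 can never be scored at that time. The documents do not establish this: Table 1 places the 12-month items inside the Sustainability and Reinforcing Phase, and Study interventions describes a reinforcing stage that begins in week five, with email support over the following 12 months. The intervention can be read as ending when that phase ends.

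**Conclusion.** The point holds for the sensitivity analysis as written. The fidelity covariate is undefined in one arm. Entered on its raw scale, it either removes that arm or turns the arm coefficient into an extrapolation to zero fidelity, with an SE about 3 to 8 times larger and an estimate driven towards 0, or below it, when benefit runs through fidelity. That range rests on 20 units per arm, comparison units coded 0, and the assumed fidelity mean of 16 to 20 and SD of 2 to 4. Follow-up length of admission is a possible consequence of the intervention, so adjusting for it may bias the total effect, by an amount the documents cannot determine.

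A reader might take this as a flaw in the trial's main result. It is not: the primary model and the sample size do not use either covariate. The point is worth settling in the statistical analysis plan, but it does not threaten the primary analysis.

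**What to change.** Remove the fidelity score from the between-arm model. Report instead, within intervention units only, the association of fidelity with the unit's mean Time Use Diary score at follow-up given its baseline mean, and label it a non-randomised comparison.

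Drop follow-up length of admission from the treatment-effect sensitivity model, or replace it with the unit's mean length of current admission at baseline, which is already collected. The small downside of the replacement is that it does not describe the stay of the residents present at follow-up.

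The cost is a change of wording in an analysis plan that the article says is still to be developed, plus a little analysis work. No new data are needed.

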### Cost effectiveness of the GetREAL intervention

Costs of care at follow-up are calculated by combining service use data collected using the Client Service Receipt Inventory combined with national unit costs and an estimate of the extra resources required for the GetREAL staff training. Cost-effectiveness of the GetREAL intervention will be assessed by combining service costs with the primary outcome (assessed using the Time Use Diary [31]) using an incremental cost-effectiveness ratio. This will show the extra cost incurred for the intervention to achieve an extra 1% of time spent in activities.

There will be uncertainty in the cost-effectiveness results obtained which we will address using cost-effectiveness planes. This will involve producing a large number of estimates of cost and outcome differences using bootstrapped regression models and plotting each pair of differences in the form of a scatter plot. This will indicate the likelihood that compared to the comparison group the intervention produces (i) higher costs and worse outcomes, (ii) higher costs and better outcomes, (iii) lower costs and worse outcomes, and (iv) lower costs and better outcomes. In addition, we will conduct sensitivity analyses around key unit costs to see what impact changing these has on the total costs and cost-effectiveness.

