## Methods

### Trial design

This is a two-arm, cluster randomised trial in which inpatient mental health rehabilitation units are the unit of randomisation. The cluster design prevents potential “contamination” of the intervention between trial arms (if, for example, staff who had received the training at a unit randomised to receive the training were to move to a comparison unit). The trial has been approved by the South East Essex Research Ethics Committee (Ref. 09/H1102/45) and is registered with Current Controlled Trials (Ref ISRCTN25898179) http://www.controlled-trials.com/ISRCTN25898179.

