### Primary outcome

The primary outcome is the degree to which service users are engaged in activity over a given week as assessed using the Time Use Diary [31]. This measure assesses service users’ activities over the previous week during four periods each day; morning, lunchtime, afternoon and evening. The degree of engagement in activity as well as the complexity of the activity is rated on a scale of 0 to 4 for each time period, giving a maximum possible score of 112. The diary is completed retrospectively during a structured interview with the service user. The scale has demonstrated good inter-rater reliability and has been validated [31]. If service users lack capacity to give informed consent to participate in a face to face interview, information about their activities in the preceding week is gathered from the case records and discussions with their primary nurse.

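### The cost-effectiveness ratio is labelled as cost per one per cent of activity time, but the Time Use Diary score behind it is not a measure of time

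*Protocol article*

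**What the plan says.** The article's section on the cost effectiveness of the GetREAL intervention takes its measure of effect directly from the trial's primary outcome. Cost-effectiveness is to be "assessed by combining service costs with the primary outcome (assessed using the Time Use Diary [31]) using an incremental cost-effectiveness ratio". The next sentence fixes the unit of the result: "This will show the extra cost incurred for the intervention to achieve an extra 1% of time spent in activities".

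The Primary outcome section describes what the diary yields. It covers "activities over the previous week during four periods each day; morning, lunchtime, afternoon and evening". On the scoring it says: "The degree of engagement in activity as well as the complexity of the activity is rated on a scale of 0 to 4". One such rating is given per period, and the maximum is 112. The Statistical analysis section models this score. No section gives a rule for turning it into minutes, hours or a percentage of time.

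**The concern.** The numerator of the ratio is a cost difference and the denominator is a difference in Time Use Diary score. The article then gives that denominator a unit, percentage of time, that the score as described does not carry. A rating that combines how engaged someone was with how complex the activity was can change when the time spent does not, and the same total can reflect very different amounts of activity.

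The stake is how the result will be read. Cost-effectiveness is part of the stated aim and one of the listed objectives, and this is the only cost-effectiveness ratio the article specifies. The Discussion links the findings to investment in these services and to a national rollout. A figure presented as cost per percentage point of activity time invites service planners to read a rating-scale gain as hours of activity bought.

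**Working it through.** **Inputs, all from the Primary outcome section.** Four periods per day; recall over one week, so seven days; each period rated 0 to 4; stated maximum 112. One assumption is needed for the illustrations: a rating above 0 means some activity in that period. The article does not print the rating anchors.

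**Reproducing the stated maximum.** 4 periods × 7 days = 28 ratings, and 28 × 4 points = 112. This agrees with the article, so the score is the plain sum of 28 ratings.

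**What 1% could mean on this scale.**
- 1% of the maximum score: 0.01 × 112 = 1.12 points.
- Share of periods: one whole period is 1/28 = 3.6% of the periods covered.

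Neither is 1% of time. The first is a share of a weighted rating sum. The second counts periods, and the article gives no length for a period.

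**Same score, different amount of activity.**

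| Pattern over the week | Score | Share of maximum | Periods with activity |
|---|---|---|---|
| All 28 periods rated 1 | 28 × 1 = 28 | 28/112 = 25% | 28/28 = 100% |
| 7 periods rated 4, 21 rated 0 | 7 × 4 = 28 | 28/112 = 25% | 7/28 = 25% |

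**Same gain, different change in activity.** Take a gain of 4 points, which is 4/112 = 3.6% of the maximum.
- Four periods already active each move up one rating: change in active periods 0/28 = 0%.
- One inactive period becomes rated 4: 1/28 = 3.6%.
- Four inactive periods each become rated 1: 4/28 = 14.3%.

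So a difference in score does not determine a difference in the share of periods with activity, and still less in time.

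**What can be computed.** With C for mean cost and E for mean score, the ratio per point is (C1 − C0)/(E1 − E0). Expressed per 1% of the maximum, the denominator becomes (E1 − E0)/1.12, so the ratio is 1.12 times the ratio per point. This is multiplication by a positive constant. It leaves the sign of each cost and effect difference unchanged, and so leaves the proportion of bootstrap pairs in each quadrant unchanged. No value of the ratio itself can be given, because the article contains no cost or effect figures.

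**The case against.** The strongest reply is that the sentence only interprets the ratio. The calculation is set out in the sentence before it, as service costs combined with the Time Use Diary outcome, and it can be carried out per point. Moving from points to per cent of maximum is a linear rescaling. The economic result is listed in the abstract among the secondary outcomes, and nothing in the primary analysis, sample size or data collection depends on it. All of this stands and limits the size of the problem. It does not remove it, because the unit is the part of the ratio that decision makers read.

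It could also be said that the engagement element of the rating may partly reflect how much of a period was occupied. That is possible, but complexity enters the same 0 to 4 rating, so the total would still not be a percentage of time.

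Two stronger readings are tempting, and the article supports neither.

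- A reader might infer that the ratio cannot be computed at all. It can, from the same data, per score point. Only the per-cent-of-time unit is unobtainable from the score.
- A reader might infer from "estimates of cost and outcome differences using bootstrapped regression models" that individuals will be resampled without regard to units, in what is a "cluster randomised trial in which inpatient mental health rehabilitation units are the unit of randomisation", so that the scatter on the plane would be too narrow. The article does not say this. The phrase is compatible with resampling whole units. Clustering is allowed for wherever model detail is given: in the sample size, in the random effects model for the primary outcome, and in the models for secondary outcomes at service user level. Further analysis detail is deferred to a full statistical analysis plan that is not shown, and the resampling unit is the kind of detail an article leaves there. How much such a bootstrap would understate uncertainty in costs would also depend on a cost ICC that the article does not give.

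**Conclusion.** The point holds as an error in the stated unit of the ratio. The economic section promises a cost per percentage of time, and the outcome it names is a 0 to 112 sum of ratings that mix engagement with complexity. On that scale 1% of the maximum is 1.12 points, and one score can correspond to activity in anything from 25% to 100% of periods, as the 28-point example shows. Followed as written, the plan would report its only specified cost-effectiveness ratio under the wrong label.

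The effect is confined to the reporting and interpretation of that ratio. On the score scale, the quadrant probabilities are the same whether the ratio is expressed per point or per 1% of the maximum, and the primary analysis is untouched. The conclusion rests on the article's own description of the diary. The examples also assume that a rating above 0 denotes some activity.

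**What to change.** In the section on the cost effectiveness of the GetREAL intervention, delete the reference to a percentage of time and define the ratio as the extra cost per one-point gain in Time Use Diary score. If a percentage is preferred, state it per 1% of the maximum score, which is 1.12 points, and label it in those words.

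If a ratio based on time is wanted, specify a separate outcome in advance, such as the share of the 28 periods with activity, together with the rating that counts as activity and how the share is derived. It should be reported as a share of periods unless period lengths are also defined. It would be a different measure of effect, so its quadrant probabilities would have to be produced separately.

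The score-based correction is one sentence. It needs no new data and no change to the primary analysis.

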### Research objectives

The aim of this study is to investigate the clinical and cost effectiveness of a staff training intervention (the “GetREAL” intervention) to increase service users’ engagement in activities.

The objectives are to:

•Investigate whether the GetREAL staff training intervention is associated with greater service user activity.

•Determine whether the GetREAL staff training intervention is associated with improved clinical outcomes.

•Examine whether the GetREAL staff training intervention is associated with improved social outcomes.

•Investigate whether the GetREAL staff training intervention is associated with improvement in the quality of mental health rehabilitation units.

•Investigate whether the GetREAL staff training intervention is a cost-effective approach to improving service users’ engagement in activities.

Our primary objective is based on ratings of service users’ activity 12 months after the staff training intervention is delivered, in order to understand whether it impacts on sustained change in the unit’s practices related to service user activities.

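### Uncertainty around the cost-effectiveness ratio is to be read only as quadrant likelihoods, which do not show how probable it is that the training is cost-effective if it costs more and works better

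*Protocol article*

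**What the plan says.** Under Research objectives, the protocol article sets out to "Investigate whether the GetREAL staff training intervention is a cost-effective approach to improving service users’ engagement in activities".

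The section Cost effectiveness of the GetREAL intervention gives the method in four steps:

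- **Main measure.** Service costs, including "an estimate of the extra resources required for the GetREAL staff training", are combined with the primary outcome "using an incremental cost-effectiveness ratio". Its unit is stated: "This will show the extra cost incurred for the intervention to achieve an extra 1% of time spent in activities".
- **Uncertainty.** "There will be uncertainty in the cost-effectiveness results obtained which we will address using cost-effectiveness planes". The planes are built by "producing a large number of estimates of cost and outcome differences using bootstrapped regression models and plotting each pair of differences" as a scatter plot.
- **Reading of the plane.** "This will indicate the likelihood that compared to the comparison group the intervention produces (i) higher costs and worse outcomes", followed by the three other combinations of cost and outcome.
- **Sensitivity.** "we will conduct sensitivity analyses around key unit costs to see what impact changing these has on the total costs and cost-effectiveness".

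The section gives no value, or range of values, for an extra 1% of time in activities.

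**The concern.** Two of the four quadrants settle the question by themselves: cheaper and better, and dearer and worse. The other two do not. In the dearer-and-better quadrant, a replicate counts as cost-effective only if the gain in activity is worth its extra cost, and the quadrant share does not record which replicates meet that condition.

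The dearer-and-better case is a realistic one to plan for, since the cost of the training is added to the intervention arm and the training is meant to raise activity. If the results fall there, the article's stated output would be a ratio, a scatter and a large share in one quadrant. None of these reports how probable it is that the training is cost-effective at a given value of activity. The Discussion looks ahead to a possible national rollout, and that decision would turn on this probability.

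**Working it through.** The cost-effectiveness section states no figure to reproduce, so the check is an illustration. All its inputs are assumed and none comes from the article.

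**Inputs (assumed).** Cost difference C: mean 500 currency units, SE 250. Outcome difference E: mean 4, SE 2, in the ICER's unit (percentage points of time in activities). Both normal and independent. L is the value placed on one extra 1% of time in activities.

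**Step 1: ICER.** 500 / 4 = 125 per extra 1%.

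**Step 2: quadrant shares.** P(C > 0) = Φ(500/250) = Φ(2) = 0.977, and P(E > 0) = Φ(4/2) = Φ(2) = 0.977.

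| Quadrant | Calculation | Share |
|---|---|---|
| Higher cost, better | 0.977 × 0.977 | 95.5% |
| Lower cost, better | 0.023 × 0.977 | 2.2% |
| Higher cost, worse | 0.977 × 0.023 | 2.2% |
| Lower cost, worse | 0.023 × 0.023 | under 0.1% |

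**Step 3: probability of being cost-effective.** Net benefit is L × E − C. Under the same assumptions,

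P(net benefit > 0) = Φ[(4L − 500) / √((2L)² + 250²)].

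| L | Calculation | Probability |
|---|---|---|
| 50 | Φ(−300 / 269.3) = Φ(−1.11) | 13% |
| 125 | Φ(0) | 50% |
| 500 | Φ(1500 / 1030.8) = Φ(1.46) | 93% |

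The quadrant table is the same in all three rows, because L does not enter it.

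**Step 4: what the planned outputs do fix.** At L = 0 the probability is P(C < 0), the sum of the two lower-cost quadrants, about 2.3%. As L grows it tends to P(E > 0), the sum of the two better-outcome quadrants, about 97.7%. The ICER marks the 50% point here. The quadrant shares therefore give the two ends of the curve and the ICER roughly its middle. The probability at any other value of activity is not reported.

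**Step 5: other assumed inputs.** Keep the cost difference at 500 (SE 250) and take an outcome difference of 2.8 with SE 1. A true difference of 2.8 SEs corresponds to 80% power at a two-sided 5% level (1.96 + 0.84 = 2.80; the article does not state the level). The shares are then 97.5% higher cost and better, 2.3% lower cost and better, 0.3% higher cost and worse, and under 0.1% lower cost and worse. The probability is Φ[(2.8L − 500) / √(L² + 250²)]: 8% at L = 50, 50% at L = 179 (500 / 2.8), 91% at L = 400 and 97% at L = 600. The pattern is the same.

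**The case against.** Several points can be made for the plan, and most of them stand in part.

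- **The ICER is the main measure.** A reader might infer that quadrant shares alone are to answer the objective. The article does not support that: the ratio is the stated assessment, and the plane describes uncertainty around it.
- **The scatter shows the whole joint distribution.** Anyone can draw a value line through it. This is true, and it is why the remedy is cheap. But the article says what the plot will be used to indicate, and that is four likelihoods.
- **An unstable ratio.** One might complain that the ICER misbehaves when the outcome difference is near zero. The plan largely avoids this by bootstrapping and plotting pairs of differences; it does not propose an interval for the ratio.
- **Costs may fall.** A reader might take dearer-and-better as the expected result. The article does not predict it. The Abstract and Background hope for less hospital treatment and put a one-week shorter mean stay at about 2% of the annual budget. If the training proved cheaper and better, the quadrant reading would answer the objective directly.
- **A full analysis plan is promised.** It could add this summary, so its mere absence from the article would be no finding. The point rests on what the article does fix, namely quadrant likelihoods as the reading of uncertainty, with only unit costs varied.
- **Net benefit also leaves the value to the reader.** This is so, and the 50% point roughly repeats the ICER. The rest of the curve is new information: the probability at each value, reported nowhere else in the stated plan.

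**Conclusion.** The point holds in limited form. The ICER and the plane are sound choices, and nothing in the section is wrong as arithmetic. The weakness is in the stated reading of uncertainty. If the replicates fall mainly in the higher-cost, better-outcome quadrant, their share cannot say how probable it is that the training is cost-effective at any given value of activity.

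In the illustration, one quadrant table goes with probabilities from 13% to 93% as the value per 1% of activity moves from 50 to 500. Those figures rest on assumed means, SEs, normality and independence, and are not an estimate for this trial. The qualitative conclusion does not depend on them, because quadrant shares contain no value per unit of activity. It would be too strong to say that the plan leaves its cost-effectiveness objective unanswered: the ICER and the plotted pairs would still be reported, and other quadrants could settle the matter. This is a worthwhile improvement of low severity.

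**What to change.** Keep the ICER as the main measure and the plane as the display. From the same bootstrap replicates, also report the probability that net benefit (value per 1% of activity × outcome difference − cost difference) exceeds zero, as a curve over a range of values.

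State that range in the full analysis plan before results are seen, so that a favourable value is not chosen afterwards. Express it in the ICER's own unit, an extra 1% of time in activities. The Time Use Diary is scored out of 112, so a value per diary point would not carry over unchanged.

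The cost is a few lines of analysis code on replicates already planned. No new data are needed.
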